##### Who Provided

In this study, a multidisciplinary team comprising UX experts, clinical researchers (psychologists and researchers with experience in social sciences), and support personnel will be involved in the implementation of the study. All members hold relevant experience in EU health projects and eHealth research and are experienced in planning, implementing, and analyzing clinical trials.

##### How

Within the study, AIT’s digital coaching app will be provided to the participants. Participants will be provided with a link to install the app on their own smartphones. The app will be provided individually to all participants in the study.

##### Where

Sample group participants will be using their digital coach mobile app at their private homes in Austria and Belgium. This RI is classified as a combination of distributed (ie, private homes) and virtual (ie, mobile app) facilities.

##### When and How Much

The AIT’s digital coaching app will be provided to the participants over a duration of 8 weeks. For data collection, 2 face-to-face sessions (each approximately 2 hours) will be scheduled with participants: 1 just before the beginning of the study and 1 at the end after 8 weeks of use.

#### Case Study 2: Net Zero Energy Buildings Smart Home Living Lab

##### Why

The aim of this feasibility and acceptability study is to evaluate the impact of physical and cognitive activity performance of older adults in a smart home Living Lab environment using a combined approach of virtual apps and several wearable sensors. This particular small-scale pilot study envisages showing us the benefits of specific types of physical and cognitive exercises combined with Living Lab technological advances. Moreover, the study will also analyze the extent to which it can influence individuals’ self-efficacy and well-being by motivating older adults to practice a healthy lifestyle. The monitoring of the effects of the virtual coach app use may shed light on the capability of digital coaching for helping retirees maintain (and improve) social relationships and activities that could be put at risk by their withdrawal from the workplace. Yoga exercises, on the other hand, will provide evidence of how the body reacts by monitoring parameters such as brain activity and heart rate.

##### To Whom (Sample Size and Recruitment)

A total of 15 persons will be recruited by Aristotle University of Thessaloniki through the collaboration and research community for independent living. Participants comprise cognitively intact healthy older adults aged >60 years, with the absence of dementia, severe cognitive impairment, psychiatric diseases, and severe cardiovascular problems.

##### What (Materials)

Data will be collected using the following wearable sensors: Fitbit Charge 3, Empatica E4, and Muse EEG, resulting in physiological big data such as accelerometer, heart rate, and electrodermal activity during the interventions. Chairs will be used as props during the yoga exercises when needed. The following validated questionnaires will be used: (1) UEQ, (2) System Usability Scale, and (3) Unified Theory of Acceptance and Use of Technology, along with predefined key performance indicators will be used to measure the acceptability and usability levels of the proposed protocols. The EuroQoL 5-dimensional 3-level questionnaire (Greek version) will be used to assess the participants’ quality of life. The filled-in Microsoft Excel templates will also be used as background materials and interview templates during each interview. The research protocols for each case study will be written as word documents using a structured format.

##### What (Procedures)

Before cognitive and physical exercises, focus group sessions with beneficiaries and clinicians will be organized for recruitment purposes and participant profile data and end users’ preferences and needs for the used technologies and interventions will be collected. The cognitive and physical exercises in a smart home Living Lab include the measurement of (1) financial capacity; (2) general cognitive status, memory, executive functions, and visuospatial functions; and (3) measurement of physical activity during virtual coaching and yoga exercises while participants are equipped with wearable sensors. After cognitive and physical exercises, focus group interviews will be conducted to assess participants’ experiences regarding usability and acceptance of the performed activities and technologies.

##### Who Provided

A multidisciplinary team comprising Living Lab experts, health care personnel, and gym assistants will participate in the participant recruitment, exercise design, and safety standard definition. Focus groups and questionnaire administration will be managed by a well-coordinated group of experienced Living Lab researchers, with 4 to 5 people taking part in the VITALISE project and having considerable experience in planning and implementing Living Lab research projects and protocols.

##### How

Scheduled visits into a smart home Living Lab will be planned for each participant. All participants will attend all cognitive and physical exercises led by a virtual instructor (exercises 1-3) or a person (exercise 4) in the following order while wearing the Fitbit Charge 3 and Empatica E4 wristband sensors: (1) assessment of participants’ financial capacity using tailored simulated Banking App [25], (2) evaluation of their general cognitive status, memory, executive functions, and visuospatial functions through the Virtual Supermarket app [26]—a simple virtual reality task running on tablet devices or PC for differentiating between MCI patients and healthy older adults, (3) implementation of the virtual coach application [27] for physical activity promotion and (4) applying a yoga session where participants will also wear the Muse EEG during the “body scanning” and “relaxation exercises” as part of the yoga protocol to obtain brain activity during these particular states. After cognitive and physical exercises, focus groups interviews will be conducted to assess participants’ experiences regarding usability and acceptance of the performed activities and technologies.

##### Where

Cognitive and physical exercise interventions will take place in the smart home Living Lab environment equipped with various technologies described previously. Face-to-face focus group sessions will be organized in meeting rooms for vaccinated individuals, whereas for the others, meetings will take place on web-based platforms such as Google Meets or Zoom videoconference.

##### When and How Much

Scheduled visits will be planned for each participant to visit a smart home Living Lab during the spring to summer of 2022. The cognitive and physical exercises will be conducted once, and their durations will be as follows: (1) simulated banking exercise for 5 minutes, (2) virtual supermarket exercise for 30 minutes, (3) virtual physical exercises coaching for 10 minutes, and (4) yoga sessions at a slow but gradually increasing pace, including breathing practice for 10 minutes, chair poses for 15 to 20 minutes, standing poses 10 to 15 minutes, floor poses 15 minutes, and a supine resting pose (Shavasana) for 10 minutes.

##### Tailoring

The interventions will be tailored for all 20 participants. Furthermore, the virtual app used during the interventions will be used in personalized mode to bring innovation.

#### Case Study 3: UX With Gradior Active for Physical Training Reinforcing Dual Task Performance

##### Why

The general aim of this case study is to test the Gradior Active prototype by assessing its usability, learnability, acceptance, and the overall experience of participants, especially in terms of how easy and pleasing it is to use or its perceived utility when embedded in active and healthy aging programs. Collection of UX during an 8-week program implementing the current Gradior Active prototype will be of most importance for the second objective, which is focused on performing a cocreation sprint to understand the challenges for optimizing the program and its implementation in real settings and services (eg, exploring ideal workflows). Ultimately, the case study results will be used to understand what is most important for the UX perspective and for developing big data–driven hybrid personas through the initially described harmonized research protocol.

##### To Whom (Sample Size and Recruitment)

A total of 30 older adults will be recruited through the INTRAS memory clinic and neuropsychological rehabilitation center customers. INTRAS has its own pre-existing testing panel of patients and participants in the active and healthy aging programs, as well as established groups of experts by experience (groups of older adults who, considering their motivations, participate in user-driven design and innovation processes). Participation will be voluntary and will follow best practices in terms of clear information in the information sheet and procedure and informed consent, accomplishing the General Data Protection Regulation, national regulations, and cognitive accessibility parameters. Participants will pertain to 2 groups of older adults aged >65 years: group A, comprising older adults with subjective complaints (for primary prevention), and group B, comprising older adults with mild physical impairment. Exclusion criteria will include participants with sensory or physical impairments that make it very difficult to use the devices (significant hearing or visual impairments) or any nutritional disorder, psychiatric conditions, or neurological problems that make the person unable to participate in the study.

##### What (Materials)

In this study, Gradior Active will be provided to the participants. This is a system for physical and cognitive training that combines motion and cognitive activities with independent and unrelated purposes (*Dual Task*). It incorporates controlled physical exercises (aerobic, strength, balance, and flexibility exercises) using motion capture technologies (Microsoft Kinect). The software comprises a Kinect v2 (Microsoft), a computer and a good size screen or projector, and a server component providing the content and collecting the data.

The program provides step-by-step instructions for the participants, and the sessions will be performed with the support of an experienced professional (eg, clinical psychologist or neuropsychologist). In total, 2 to 3 units will be installed and configured in the INTRAS clinic facilities with the information technology team support. Informed consent will be provided in paper form; questionnaires for collecting quantitative data and UX diaries will be provided either in paper form or as a link to a web-based questionnaire. During the cocreation sessions, easy-to-use digital tools such as Kahoot! (Kahoot ASA) to facilitate social interaction and pleasing moments in the group will also be considered.

##### What (Procedures)

The study follows a mixed methods design in which qualitative and quantitative data will be collected. To determine the effects of Gradior Active on the 8-week term, 2 measurements (T0 and T1) will be conducted using standardized tests. Thus, 2 face-to-face sessions will be scheduled with participants: 1 just before the beginning of the study and 1 at the end after 8 weeks of use. At baseline (T0, before the start of the intervention), demographic data will be collected. The following outcomes will also be measured both at baseline (T0) and after the end of the intervention (T1): patient-reported outcome measures, including health and well-being (Short Form-36 version 2), social life (Lubben scale), Geriatric Depression Scale (GDS), Physical Status Scale (Rapid Assessment of Physical Activity), and (4) Borg Scale of Perceived Exertion; and patient-reported experience measures, including UX (UEQ) and usability and acceptance (System Usability Scale).

##### Who Provided

INTRAS counts with a multidisciplinary team comprising clinical researchers and technologists widely familiar with UX research and studies with digital health and well-being solutions and experts in the participatory methodologies that will be involved in the implementation of the study. All members hold relevant experience in EU health projects, eHealth research, and planning, implementation, and analysis of clinical trials. The study will be coordinated by a psychologist (panel manager), neuropsychologist (scientific coordinator), and gerontologist (project manager) with >10 years of experience in clinical services, (EU) health projects, eHealth research, user research, Living Lab research, and implementation and analysis of real-life tests.

##### How

The study evaluations will be set up in a single site in Spain with a quasi-experimental format without a control group, where each participant acts as their own control through the pre- and postdesign. The study is divided into 2 phases to accomplish the indicated aims. The first phase collects UX with the Gradior Active prototype during the 8-week testing period. The second phase will be focused on a cocreation sprint bringing the individual experience to a group discussion to understand what is linked to perceived value and opportunities for improvement based on value-driven brainstorming exercises (from the current prototype to ideal service offer). These interactive group sessions will include icebreakers, co-design methods, and adequate tools for the purposes. Testing sessions with Gradior Active will be performed individually and in a face-to-face format in the facilities of the Living Lab and INTRAS Clinic. The sessions will be supervised by an experienced therapist. Cocreation sessions will be conducted face to face and in groups. The sessions will take place with the support of 2 experienced facilitators in the INTRAS facilities. For both the stages and planned activities, COVID-19 safety protocols will be in place.

##### Where

A case study will be conducted in the INTRAS rehabilitation Living Lab in the neuropsychological rehabilitation center (with access to INTRAS care centers and memory clinics as ecologically valid environments for Living Lab activities).

##### When and How Much

In the first phase of the study, Gradior Active will be provided to the participants over a duration of 8 weeks, and participants will be oriented to perform 2 weekly sessions of 30 minutes under the supervision of experienced professionals. After the end of the intervention period, the same participants who previously tested the prototype will be invited to the 2 cocreation sessions (duration: 120 minutes).

##### Tailoring

Both the prototype testing phase and cocreation phase will be coordinated considering the participant’s availability and other relevant conditions to participate (eg, transport logistics to attend the sessions). Testing sessions with the Gradior Cognitive intervention program will be supervised by an experienced professional who can intervene to provide support as required. In principle, pre- and postinterviews with assessment and workshop interventions follow the same principles for all participants, and modifications are not preplanned. However, if a need to make modifications emerge, they can be made.

#### Cross-country Case Study 4: Multidimensional Physical Fitness Testing Protocol for Aging Persons

##### Why

With older adults, functional independence is directly dependent on physical fitness. Aging is inevitably associated with the declining functions of systems and organs (heart, lungs, blood vessels, and skeletal muscles) that determine physical fitness. However, aging is a complex process involving many variables that interact with one another, for example, lifestyle factors, chronic diseases, and genetics. Relatively little is known about the physical fitness levels needed to maintain physical independence. Many studies have shown that measurements of physical performance can predict future mobility disability, institutionalization, and mortality. Studies have also shown a strong association between measurements of physical performance and self-reported mobility disability. However, most of these prospective studies used only a few measures of physical performance or were targeted at functionally limited persons; therefore, assessments have only limited value for counseling. Therefore, this case study will develop and test a physical fitness testing protocol for older adults in real-life settings in 3 countries: Finland, Spain, and Hungary.

##### To Whom (Sample Size and Recruitment)

In Finland, the sample group will comprise older adults aged >67 years. To recruit older adults with varying physical fitness levels, the following strategy will be applied: open calls to promote free of charge physical fitness level measurement as part of a research project will be published in local newspapers and social media channels in collaboration with the local city administration responsible for older adult services. Furthermore, the collaboration will be conducted with selected nursing home administrators to recruit participants with weaker physical fitness levels directly from nursing homes. It is estimated that approximately 200 to 400 persons will be recruited via open calls and approximately 50 persons from nursing homes. In Hungary, the sample group will comprise people aged >55 years. Social media, posters in outdoor trails and fitness parks, former contact lists, and snowball sampling will be used to recruit the participants. It is estimated that 30 to 50 persons will be recruited; however, because of dropouts during the training program, only 20 are expected to take part in the posttest. In Spain, the main target sample will be men and women aged between 60 and 80 years. of Participants will be recruited in collaboration with the city council of Gernika-Lumo, local nursing homes, and retiree associations. It is estimated that 20 to 40 people will be recruited from all collaborative organizations.

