##### What (Procedures)

The following physical fitness components will be covered in the physical fitness test in Finland and Spain: cardiorespiratory endurance, muscle strength and endurance, balance, agility, speed, flexibility, and body composition. After signing the consent form and filling the quality of life questionnaire (World Health Organization Quality-of-Life Scale), the participants will go through the following measurement points step by step in selected locations (ie, sports halls, nursing homes, fitness parks, and outdoor facilities): (1) 6-minute walk test or nonexercise cardiorespiratory fitness test, (2) handgrip strength test, (3) 30-second arm curl test, (4) 30-second chair stand test, (5) Smartifier balance board test, (6) 8-foot up-and-go test, (7) backward walk test, (8) 10 m walk test, (9) chair sit-and-reach test, (10) back scratch test, (11) height and body composition measurements, and (12) peak expiratory flow measurement. In Hungary, which is used as a control group, physical fitness will be measured by following a protocol defined in the senior fitness test manual [28]. After finishing the measurement track, participants will fill the UEQ, which also includes an open text box to propose improvement suggestions or give complaints about the testing procedure.

In Hungary and Spain, the physical fitness testing battery will be used to determine the baseline (T0, before the start of the training program intervention) and conduct the postmeasure (T1) at the end of the 8-week training program. Participants’ daily activities will also be measured with the armband device for 4 days during the training period. In addition, in Spain, some of the participants will also use a smart wristband watch (Galaxy Watch 3). In Hungary, the training program will include outdoor training on fitness trails with 19 stations in a 1.5 km route. Feedback will be collected from participants after the training intervention. In Spain, outdoor training on recreational football will be performed in a network of distributed resources and public spaces. Feedback will be collected from participants after the training intervention.

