### Case Study Outcomes

#### Case Study 1

This study will allow a better understanding of how digital coaching can influence individuals’ well-being and social participation by motivating older adults to practice a healthy lifestyle. Monitoring the effects of AIT’s digital coaching app use may shed light on the capability of a digital coach for helping retirees maintain (and improve) social relationships and activities that could be put at risk by their withdrawal from the workplace. In addition, the results will also allow the optimization of the UX of deployed coaching mobile apps. By setting up this case study at 2 different sites, Belgium and Austria, specific results related to these different social and cultural contexts are also expected.

#### Case Study 2

The results of the randomized controlled trial will show that it is feasible to conduct a randomized controlled trial of yoga in a virtual and sensor-assisted Living Lab environment using the described protocol. Moreover, the collection of novel sensor data from the experiment is expected to provide insightful information about the physical and psychological status of the participants.

#### Case Study 3

The results of this study will allow the analysis of effectiveness, usability, and acceptance of the described Gradior Active intervention. It will state the pillars for evidence-based decision-making on investment in the upgrade and modernization of the prototype; at the same time, it will ensure a final co-design sprint with participants to orient the incremental development plans.

#### Case Study 4

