The main results will focus on understanding older adults’ physical fitness levels by defining and testing comprehensive testing patterns in a cross-country setting. Single test results with reference values exist; however, surprisingly, a wider understanding of older adults’ fitness levels is lacking. From prior studies, it is acknowledged that the vast majority of the participants recruited via open calls will be persons with good fitness and functioning levels. Therefore, older adults with lower physical fitness will be recruited from nursing homes to also cover more fragile and less fit older adults. By combining the daily physical activity level sensor measures and physical fitness test results, novel and insightful information about the physical status of the participant can be verified. The perceived UX of the proposed comprehensive physical fitness level research protocol will be compared with a well-established but less comprehensive protocol. It is expected that there will be no significant differences regarding UX; therefore, in the future, a more comprehensive protocol should be applied to reveal a better understanding of the older adults’ physical fitness levels. Furthermore, the pre- and posttraining period physical fitness levels will be compared in the cases of the Spain and Hungary case studies. These results are expected to reveal that the training program affects participants’ physical fitness level as well as provide suggestions from participants on how to improve the training program.

#### Case Study 5

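### Case study 4 expects to credit training with a fitness change from pre/post data that have no untrained comparator and, in Hungary, 33% to 60% expected loss at T1; case study 3 promises effectiveness without a control

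*Protocol article*

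**What the plan says.** **Case study 4.** Under To Whom, the Hungarian sample is described thus: "It is estimated that 30 to 50 persons will be recruited", but "because of dropouts during the training program, only 20 are expected to take part in the posttest". For Spain: "It is estimated that 20 to 40 people will be recruited from all collaborative organizations", with no dropout forecast. What (Procedures) places T0 and T1 around the 8-week training in Hungary and Spain only. Finland has no training programme and no T1. The same section says: "In Hungary, which is used as a control group, physical fitness will be measured" by the established senior fitness test protocol.

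The Discussion (Case Study Outcomes, Case Study 4) states that "the pre- and posttraining period physical fitness levels will be compared in the cases of the Spain and Hungary case studies" and continues: "These results are expected to reveal that the training program affects" participants' fitness level.

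**Case study 3.** How describes "a quasi-experimental format without a control group, where each participant acts as their own control". What (Procedures) sets out to determine the effects of the product over 8 weeks. The Discussion says: "The results of this study will allow the analysis of effectiveness, usability, and acceptance" of the intervention.

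**Analysis.** The data analysis section for Phase 2 is one list for all case studies. It includes paired and unpaired two-tailed t tests and nonparametric tests, and says that case studies of intervention impact measure once before and once after.

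**The concern.** Two separate weaknesses stand between these data and the conclusion expected from them.

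The first is the absence of an untrained group measured twice. Familiarity with the tests on a second attempt, and the passing of 8 weeks from a spring or summer start, can both shift the scores. Nothing in the design separates these from training.

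The second is loss between T0 and T1 in Hungary, which the article itself puts down to people leaving the training. A paired test uses only people with both values. If those who leave would have changed less than those who stay, the observed change overstates the change among everyone who started.

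At stake is a positive pre/post difference being reported as a training effect in case study 4, or as product effectiveness in case study 3, where the Discussion links the results to decisions on investing in the prototype.

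**Working it through.** **Inputs from the article.** Hungary: N = 30 to 50 recruited, 20 expected at T1. Spain: 20 to 40 recruited, no T1 figure. Case study 3: 30 recruited, no T1 figure. No effect size, SD, alpha or power is given for either case study, so there is no sample-size figure to reproduce.

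**Step 1. Implied loss in Hungary**, 1 − 20/N:
- N = 30: 1 − 20/30 = 33%
- N = 50: 1 − 20/50 = 60%

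In reverse, 20/(1 − 1/3) = 30 and 20/(1 − 0.60) = 50, so the stated counts fit together.

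**Step 2. Effect of the loss on the estimated change.** Let completers change by g on average and dropouts by f × g. The mean change in all starters is g × [20 + (N − 20)f]/N. The completer figure overstates it by

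N / [20 + (N − 20)f].

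The value of f is an assumption; the article gives nothing from which to estimate it.

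| f | N = 30 | N = 50 |
|---|---|---|
| 1 (dropouts change as much) | 30/30 = 1.0 | 50/50 = 1.0 |
| 0.75 | 30/27.5 = 1.09 | 50/42.5 = 1.18 |
| 0.5 | 30/25 = 1.20 | 50/35 = 1.43 |
| 0 (dropouts do not change) | 30/20 = 1.5 | 50/20 = 2.5 |

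For f between 1 and 0 the factor runs from 1.0 to 2.5. It is not bounded at 2.5: if dropouts decline (f = −0.5), it is 30/15 = 2.0 to 50/5 = 10. It covers attrition only. Retest gain and season come on top and cannot be sized from the article.

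**Step 3. Would a mixed model on T0 and T1 remove the problem?** With two time points, its estimated change is the completers' change + (b − 1) × (T0 mean of all − T0 mean of completers), where b is the slope of T1 on T0. If the baselines agree, this returns the completers' change. If completers start fitter and b < 1 (both assumptions), both factors of the added term are negative, so the estimate rises. The model is therefore no safeguard here.

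**Step 4. Is there a control for training?** Finland has no T1. Spain and Hungary both train. How in case study 4 explains that Hungary's different test protocol supplies a baseline for user experience, to show how the longer test track affects it. Hungary is thus a comparator for the testing protocol, not for training.

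**The case against.** The case for leaving the plan as it is has real substance.

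- **Purpose.** Case study 4 exists to develop and try out a fitness testing protocol; the training comparison is an additional item. Case study 3 aims mainly at usability and acceptance. The project calls these small-scale case studies, and the tests serve to explore possible findings and future directions. This justifies an uncontrolled design. It does not justify causal wording about what the design will show.
- **Conduct at T1.** A reader might infer that dropouts are barred from the posttest. The article only forecasts attendance; it sets no such rule, and Tailoring lets people take part selectively. The point is therefore that the invitation should be made explicit.
- **Analysis.** A completers-only analysis is nowhere prescribed, and missing-data handling may sit in a plan not shown. That is fair, but no later analysis can recover T1 values that were never collected or supply an untrained group.
- **Direction.** A reader might take 1.5 to 2.5 as the bias in this study. It holds only if every dropout's expected change is zero. That completers are fitter or more motivated is plausible but undocumented, and fitter people may have less room to gain.
- **Basis of the conclusion.** It would be wrong to say that it rests on 20 Hungarians alone; the comparison covers Spain too, where the attrition figure does not apply.
- **The control label.** A reader might take Hungary to be presented as a control for training. Read with How, the label concerns user experience. It is loose wording, not a false design claim.
- **Case study 3.** It discloses the lack of a control, predicts no effect and gives no dropout figure, so the attrition argument does not carry over. The mismatch between an uncontrolled design and a promised analysis of effectiveness remains.

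**Conclusion.** The point holds in limited form. The article expects the Spanish and Hungarian pre/post comparison to show that training affects fitness, and the design cannot support that attribution in either country because no untrained group is measured twice. In Hungary the expected loss of 33% to 60% adds a possible attrition bias of 1.0 to 2.5 fold for f from 1 to 0, relative to the change among all starters. That range depends wholly on an unknown f, and the comparison with all starters is chosen for this check; the article names no such target. For case study 3 only the missing control counts against the effectiveness wording. The designs can stand as exploratory; the conclusions drawn from them, and the approach to T1 attendance, should change.

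**What to change.** 1. **T1 attendance.** In Hungary and Spain, state that every participant with a T0 test is invited to T1 at 8 weeks whatever their training attendance, and record attendance.
2. **Reporting.** Give the pre/post change with the number missing, a baseline table of those with and without T1, and a sensitivity analysis that sets missing changes to zero. At the Hungarian forecast that analysis would turn a completer change g into 20/30 = 0.67g to 20/50 = 0.40g. Do not rely on a mixed model to remove the attrition bias.
3. **Wording.** In the Discussion for case studies 3 and 4, replace the effectiveness and training-effect statements with *pre/post change, not attributable to the intervention without a control*.
4. **Label.** In case study 4, What (Procedures), state that Hungary is the comparator for user experience of the testing protocol only, in line with How.

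The cost is small: wording changes, attendance records and some additional T1 invitations at an event already planned. In Hungary these number at most 30 − 20 = 10 to 50 − 20 = 30, and fewer if dropouts would be invited anyway. No new arm is needed. The price is a more modest conclusion.
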